### Data management

All participant data will be securely stored in locked cabinets and password protected files on the chief investigator’s computer at Ear Science Institute Australia. Identifiable information of participants will be kept separate from participant results on outcome measures, and only anonymous results will be analysed and reported in research outputs (i.e. journal articles, conference presentations) pertaining to this research.

### Data analysis and statistical methods

SPSS (version 26) will be used to calculate descriptive statistics for demographic data and outcome test results at pre-intervention, post-intervention, and 3-month follow-up assessments. Generalised linear mixed models (GLMMs) will be used to analyse outcome variables. Each GLMM will be assessed for statistically significant Group x Time interaction effects, main effects of Time (per group), and pairwise contrasts. Age effects on cognitive training will be considered in the statistical analysis and results will be discussed accordingly.

Following a wave of recent criticism drawing attention to the limitations of the frequentist approach (i.e. *p* values and alpha levels) of statistical analysis, there has been increasing recommendations for researchers to report Bayes factors to support the interpretation of their findings [33]. Within the frequentist approach, it is most frequently misunderstood that a statistically significant *p* value (i.e. *p* ≤ .05) provides evidence in support of an alternative hypothesis, whereas a statistically significant *p* value can only provide evidence to disprove the null hypothesis and cannot suggest whether the observed data supports an alternative hypothesis [33]. Compared to the frequentist approach, however, the Bayesian framework allows researchers to quantify whether changes in their observed data favour the null hypothesis or their alternative hypothesis by considering prior odds (i.e. prior evidence of similar effects). It is therefore important that researchers report Bayes Factors alongside frequentist statistics to provide a more informative interpretation of their findings. From the GLMM results, Bayes Factors will be approximated using the Bayesian Information Criterion (BIC) from each model (i.e. H0 and H1) and reported to provide evidence of whether auditory training combined with adaptive CCT improves study outcomes to a greater extent, when compared to auditory training combined with non-adaptive (i.e. placebo) CCT.

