#### Treatment expectations

The Stanford Expectations of Treatment Scale (SETS) will be used to assess participants’ baseline expectations of their anticipated response to the treatment (i.e. cochlear implant and auditory/cognitive rehabilitation) [30]. The SETS include 10 items, with six items relating to a participants’ potential positive or negative belief of their future response to a treatment. An example item includes, “My condition will be completely resolved after treatment” and responses range from “Strongly Disagree” to “Strongly Agree”. Treatment expectations will only be recorded at baseline and performance on the SETS will be analysed in relation to study outcomes and may be controlled for in outcome results.

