### Randomisation and blinding

The first participant recruited to the trial will be randomised to either the adaptive or non-adaptive CCT group. The following participants will then be allocated to either group using minimization [31]. Participant group allocation details will be documented and stored securely by the chief investigator in a password-protected file. As a single-blind trial, participants will be blind to group allocation and it will not be possible for participants to tell from the online CCT interface which group they have been assigned to.

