### Power analysis and sample size

Evidence from our recent meta-analysis of cognitive training for adults with hearing loss reported beneficial effects ranging from small to large [17], with contributing studies including 10 to 67 participants. Using G*Power (34), an a priori power analysis was conducted to determine the required sample size when comparing two intervention groups across three measurement intervals (i.e. pre-intervention, post-intervention, and 3-month follow-up) for any of the primary outcome measures (speech/sound perception or cognition). To detect a medium effect (*f*
^2^ = .25) at an alpha of .05 and power of .90, 36 participants will need to be recruited. To account for potential 20% attrition, 44 participants (i.e. 22 per group) will be targeted for recruitment.

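### Allocation is by minimisation, but the described models do not commit to adjusting for the minimisation factors; between-group contrasts at a visit are conservative if the factors are prognostic, and Group x Time only if they predict change

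*Protocol article*

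**What the plan says.** All places are in the protocol article.

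- Randomisation and blinding: the first participant is randomised, and then "The following participants will then be allocated to either group using minimization [31". The factors are not named.
- Data analysis and statistical methods: outcomes are analysed with generalised linear mixed models, and "Each GLMM will be assessed for statistically significant Group x Time interaction effects, main effects of Time (per group), and pairwise contrasts". On age: "Age effects on cognitive training will be considered in the statistical analysis and results will be discussed accordingly". Bayes factors are approximated from the BIC of an H0 and an H1 model.
- Treatment expectations: "performance on the SETS will be analysed in relation to study outcomes and may be controlled for in outcome results".
- Power analysis and sample size: the calculation is for "comparing two intervention groups across three measurement intervals (i.e. pre-intervention, post-intervention, and 3-month follow-up"; "at an alpha of .05 and power of .90, 36 participants will need to be recruited". With attrition, "To account for potential 20% attrition, 44 participants (i.e. 22 per group) will be targeted for recruitment".

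No section ties a model term to the minimisation. Equally, no section says that the models hold nothing but Group and Time.

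**The concern.** Minimisation makes the arms alike on the chosen factors. Where a factor predicts the quantity being tested, this balance makes the treatment estimate less variable than simple randomisation would. A model without the factor still counts its variation as residual noise. The standard error is then too large, the test runs below its nominal level, and the precision gained by the allocation is not used.

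With 36 to 44 participants that precision matters. The likely harm is that a real benefit is reported as no difference. A false claim of benefit is not the risk here.

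The described tests do not all respond alike. A contrast between arms at one visit is exposed to any factor that predicts outcome level. Group x Time is a within-person comparison, so a stable effect of a factor cancels from it, and only a factor that predicts change matters. For the same reason, adding the factors as main effects alone would leave the Group x Time test essentially as it was.

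**Working it through.** **1. The plan's own figure.** Inputs from Power analysis and sample size: 2 groups, 3 measurements, alpha .05, power .90, N = 36 and a medium effect. Assumed, because not stated: f = .25 (the article prints f² = .25, but the Group x Time test at f = .5 would need only 12 participants), correlation .5 between visits, sphericity.

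- Noncentrality = N·f²·m/(1 − ρ) = 36 × 0.0625 × 3 / 0.5 = 13.5.
- Degrees of freedom = (2−1)(3−1) = 2 and (36−2)(3−1) = 68.
- Power = .906 at N = 36 and .888 at N = 34, so 36 is reproduced. The test that fits the stated sample size is Group x Time.

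With total SD 1 and the effect spread as T0 against T1 and T2, f = .25 is a difference in T0-to-T1 change of 2 × 0.25 × √3 × 3/√6 = 1.06. The SD of change is √(2 × (1 − .5)) = 1, so the planned effect is 1.06 SD of change.

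**2. Expected size by formula.** Let the factors explain a share R² of the variance of the tested quantity. Under perfect balance the true standard error is about √(1 − R²) times the one the unadjusted model reports. Type I error is then roughly the two-sided t tail (34 df) beyond 2.032/√(1 − R²):

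| R² | 2.032/√(1−R²) | approximate type I error |
|---|---|---|
| .05 | 2.085 | 4.5% |
| .10 | 2.142 | 3.9% |
| .25 | 2.347 | 2.5% |
| .30 | 2.429 | 2.1% |
| .45 | 2.740 | 1.0% |

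**3. Simulation, change contrast (1 df).** N = 36, deterministic minimisation on two assumed binary factors, change SD 1; 8,000 null and 4,000 power replicates (Monte Carlo SE about 0.2 and 0.5 points). Each cell is without v with the factors:

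| R² of change | type I error, % | power at 1.06 SD, % | at 0.8 SD, % | at 0.5 SD, % |
|---|---|---|---|---|
| .05 | 4.3 v 4.7 | 87.2 v 88.1 | 65.6 v 66.9 | 30.3 v 32.1 |
| .10 | 4.2 v 5.1 | 88.1 v 90.2 | 64.3 v 68.3 | 29.2 v 32.3 |
| .25 | 2.8 v 5.2 | 89.1 v 94.4 | 65.8 v 76.5 | 28.2 v 38.6 |

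A separate run with two and three factors gave type I error of about 2.4 to 3.0% without them at R² = .25.

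**4. Simulation, Group x Time F test (2 df).** N = 36, two binary factors, 6,000 replicates per setting. Each cell is without v with factor-by-Time terms:

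| Factors predict | type I error, % | power at f = .25, % |
|---|---|---|
| level only, 30% of variance | 5.1 v 5.3 | 90.3 v 90.0 |
| level only, 45% | 5.2 v 5.1 | 90.4 v 90.2 |
| 10% of change | 4.2 v 4.8 | 90.4 v 91.7 |
| 30% of change | 3.1 v 5.3 | 93.3 v 95.9 |
| 50% of change | 2.2 v 5.5 | 96.0 v 98.7 |

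The level-only rows show no effect. In the change rows the loss on the 2-df test is about 1 to 3 points, because here the factors act on only one of its two contrasts. If they explained the same share of both, step 1 with noncentrality 13.5/(1 − R²) and 64 denominator df gives .920, .933 and .968 for R² = .05, .10 and .25, against .906.

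**5. Simulation, between-group contrast at T1.** Same runs as step 4, level-only settings. With the factors explaining 30% or 45% of outcome variance, type I error is 2.2% or 1.1% without them and 5.0% with them. Power is 13.5% or 10.8% without and 22.6% or 28.4% with. These powers are low because the simulated pattern puts only 2 × 0.25 × √3/√6 = 0.35 SD between the arms at T1. They show direction, not planned power.

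**6. Cost of adjusting.** Change contrast at 1.06 SD, 3,000 replicates (Monte Carlo SE about 0.6 points), power without v with the factors:

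| Factors | R² = 0 | .05 | .10 |
|---|---|---|---|
| four | 86.6 v 85.2 | 88.5 v 88.3 | 89.1 v 90.5 |
| six | 87.0 v 85.9 | 87.4 v 86.8 | 87.9 v 88.7 |

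**The case against.** The strongest reply is that this rests on silence. The analysis section says what each model is assessed for, which is not a full list of its terms, and a condensed article may leave covariates to an analysis plan that is not shown. Age effects are to be considered and treatment expectations may be controlled for. Because the factors are unnamed, either could be one of them. This stands against reading the article as fixing models with only Group and Time, or as excluding the factors. A reader might infer that, but the text does not say it. What remains is that the article does speak about covariates, leaves both optional and links neither to the allocation.

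A reader might also infer that every test in the plan runs below 5%. Step 4 contradicts this for the Group x Time test when the factors predict level only, and the article contains nothing that shows they predict change. Its interest in age effects on training makes such prediction conceivable, no more.

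It is also fair that the gain at the planned effect is small, that the direction is conservative, and that with four or six weak factors adjustment gains nothing or loses slightly. These points lower the severity. They do not remove the case for analysing by what the allocation balances on.

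**Conclusion.** The point holds in conditional form. Allocation is by minimisation and the described models do not commit to the factors.

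- Between-group contrasts at T1 or T2 are conservative and lose power if the factors are prognostic. The article does not say which pairs its pairwise contrasts compare.
- Group x Time is affected only if the factors predict change, and is essentially unchanged if they predict level.
- For the change contrast at N = 36, type I error is about 4% at 10% of variance explained and 2.5 to 3% at 25%. Power at the planned effect is lower by about 2 to 5 points (about 1 to 3 on the 2-df test in step 4), with little or no difference at 5% or less. The roughly 10-point losses need both 25% explained and an effect smaller than planned.

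The number and type of factors, their strength, deterministic minimisation, the correlation of .5 and sphericity are all assumptions. Severity is low to moderate.

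**What to change.** In Data analysis and statistical methods, state that every primary and secondary model includes the factors used in the minimisation:

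- with their Time interactions wherever Group x Time is tested, or as covariates for the T1 and T2 outcomes if T0 is itself a covariate;
- with any continuous factor entered as continuous, not by its minimisation category;
- with the same factor terms in both the H0 and the H1 model, so that the BIC comparison isolates the treatment effect.

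Report the version without the factors as a sensitivity analysis.

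This is one sentence and needs no new data, since the factor values must be collected to run the minimisation. It uses a few degrees of freedom, which by step 6 costs up to about 1 point of power if there are several weakly prognostic factors.

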## Methods/design

A single-blind, head-to-head, randomised controlled trial (RCT) design will be used to determine whether auditory training combined with adaptive CCT will elicit greater improvement in study outcomes in adult cochlear implant recipients, when compared to auditory training combined with non-adaptive (i.e. placebo) CCT (see Fig. 1). Following enrolment into the study, participants will complete a pre-intervention assessment (*T*_0_) of speech/sound perception, cognition, mood, and quality of life, followed by their cochlear implant surgery and randomisation to either the intervention group (auditory training + adaptive CCT) or the control group (auditory training + non-adaptive CCT). Participants will then complete the 12-week training intervention followed by a post-intervention assessment (*T*_1_) and 3-month follow-up assessment (*T*_2_) involving the same outcomes measured at pre-intervention. Previous cognitive training studies have used a training period of 4–8 weeks [17]. For the current study, a training intervention of 12 weeks has been chosen to ensure participants gain the full benefits of the training. A follow-up at 3 months has been deemed appropriate to ensure continued participant interest and prevent high attrition rates. The use of an active control group will ensure that participants are blind to whether they are receiving adaptive or non-adaptive training, which helps eliminate potential placebo effects of training. The RCT will be conducted at Ear Science Institute Australia, Perth, Western Australia. Ethics approval for the study was received from the University of Western Australia Human Research Ethics Committee (RA/4/20/5287), and the trial was registered with the Australian and New Zealand Clinical Trials Registry (ACTRN12619000609156).

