### Test procedure

Participants who meet the clinical criteria for a cochlear implant will be recruited into the study. Participants will complete audiometric testing and speech/sound perception assessment within the 12 months preceding surgery and complete the pre-intervention cognitive, mood, and quality of life assessment within 1 week prior to implant. Participants will have the option to complete the pre-intervention assessment in their home or at the Ear Science Institute Australia at a time that is most convenient to them. Following cochlear implant surgery and recovery, participants will attend their ‘switch-on’ appointment where they will be provided with the standardised auditory training material by their implant audiologist. Following ‘switch-on’ appointments, participants will be randomised to either the adaptive or non-adaptive CCT group and the lead researcher will schedule a time within the same week to visit participant homes to set up the CCT equipment. As the CCT platform, Brain HQ will be delivered via the internet to participant’s home computers and the lead researcher will spend time explaining and demonstrating how to use the platform. Participant adherence to the training will be automatically monitored by the program and remotely by the lead researcher. Participants will be sent regular text messages during the intervention as polite reminders to complete their CCT sessions. Following completion of the training, participants will complete audiometric testing and a post-intervention assessment of their speech/sound perception, cognition, mood, and quality of life. The same outcomes will also be measured at the 3-month follow-up assessment to provide evidence of long-term benefits of CCT.

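### The Group x Time test treats the pre-randomisation T0 score as a third outcome instead of adjusting for it; the test is valid but less precise than the same data allow

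*Protocol article*

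**What the plan says.** Under Data analysis and statistical methods, the Protocol article analyses the outcomes with generalised linear mixed models and states: "Each GLMM will be assessed for statistically significant Group x Time interaction effects". The same sentence adds main effects of time within each group and pairwise contrasts.

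Under Power analysis and sample size, the trial is sized for "comparing two intervention groups across three measurement intervals (i.e. pre-intervention, post-intervention, and 3-month follow-up". T0 is therefore a level of Time. The section continues: "To detect a medium effect" (printed as f² = .25) "at an alpha of .05 and power of .90, 36 participants will need to be recruited", and then "To account for potential 20% attrition, 44 participants (i.e. 22 per group) will be targeted for recruitment".

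Under Methods/design, the T0 assessment is "followed by their cochlear implant surgery and randomisation to either the intervention group", so T0 precedes allocation.

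For speech, Test procedure says: "Participants will complete audiometric testing and speech/sound perception assessment within the 12 months preceding surgery". The other T0 outcomes are taken within 1 week before implant. Sound and speech perception adds that speech is tested through hearing aids before implantation and through the speech processor afterwards.

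Nowhere is the baseline score named as a covariate, and nowhere are the groups given a common T0 mean. Age is to be considered, and treatment expectations "may be controlled for in outcome results".

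**The concern.** Because allocation follows T0, the two groups have the same expected T0 score, and any observed T0 difference is chance. An unconstrained Group x Time test over T0, T1 and T2 nevertheless estimates that difference and compares the groups on change from it. This carries the full T0 sampling error into the treatment comparison. Adjusting for T0 removes only as much of the baseline as actually predicts the later score.

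The lower the correlation between T0 and the later visits, the more a change score loses. Speech is a primary outcome, and there the listening device changes between T0 and T1 and the T0 measurement may be up to 12 months old at surgery. A low correlation is plausible for it. With 36 evaluable participants, the trial has little precision to spare.

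**Working it through.** **The article's own figure first.** Two groups by three times gives (2−1)(3−1) = 2 df for the interaction; the article does not print this number. For the repeated-measures interaction F test, λ = N·m·f²/(1−ρ) with df 2 and 2(N−2). With N = 36, m = 3, f = .25 and an assumed ρ = .5:

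λ = 36 × 3 × .0625 / .5 = 13.5, df 2 and 68, power .906.

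So N = 36 reproduces, provided the printed f² = .25 is read as f = .25 (read literally, it gives N = 12). For attrition, 36 × 1.2 = 43.2, rounded up to 44. The sizing therefore matches the three-level interaction with T0 as an outcome.

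**Variance at one visit** (unit variance, T0-T1 correlation ρ):
- change score: 2(1−ρ)
- adjusted for T0: 1−ρ²
- ratio: 2(1−ρ)/(1−ρ²) = 2/(1+ρ)

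This is 2/1.8 = 1.11 at .8, 2/1.5 = 1.33 at .5 and 2/1.3 = 1.54 at .3.

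**Power of the 2-df tests.** Take n = 18 per arm, complete data, approximately normal outcomes, and a group difference of d SD that is equal at T1 and T2. Let r₀ be the T0-post correlation and r₁₂ the T1-T2 correlation.
- Planned test, unstructured covariance: λ = n·d²/(3 − 4r₀ + r₁₂), df 2 and N−3.
- T0-adjusted joint test of the T1 and T2 group differences: λ = n·d²/(1 + r₁₂ − 2r₀²), df 2 and N−4.

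With d = 0.8, n·d² = 18 × .64 = 11.52:

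| r₀ / r₁₂ | Planned λ | Power | Adjusted λ | Power |
|---|---|---|---|---|
| .8 / .8 | 11.52/.60 = 19.20 | .97 | 11.52/.52 = 22.15 | .99 |
| .7 / .7 | 11.52/.90 = 12.80 | .87 | 11.52/.72 = 16.00 | .94 |
| .5 / .5 | 11.52/1.50 = 7.68 | .66 | 11.52/1.00 = 11.52 | .83 |
| .3 / .7 | 11.52/2.50 = 4.61 | .43 | 11.52/1.52 = 7.58 | .65 |

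With compound-symmetry df (2 and 68), the planned power at .5 is .68 instead of .66.

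**At the article's own planning effect.** Setting 18·d²/1.5 = 13.5 gives d² = 1.125, so d = 1.06 SD at both T1 and T2. With all correlations .5 and N = 36, the planned test has .89 (.906 with compound-symmetry df) and the T0-adjusted 2-df test .98.

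**Other effect patterns, all correlations .5, N = 36:**
- Effect at T1 only, 1.06 SD: planned .89, adjusted 2-df .92.
- Effect growing from 0.4 SD at T1 to 0.8 SD at T2: planned .53, adjusted 2-df .67, a 1-df adjusted test at T1 alone .27.

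The adjusted 2-df test was ahead in every pattern tried. The 1-df test at T1 was not.

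**The case against.** A Group x Time test is conventional and valid in a randomised trial with pre, post and follow-up visits, and the sample size is consistent with it. The quoted sentence also does not exclude a model with a common T0 mean, and such detail is often left to an analysis plan. This stands in part: there is no error of validity, and a reader who infers bias or an inflated type I error would be wrong. But the article does fix the interaction as the test and T0 as one of its time levels, and it names no baseline adjustment. As written, the less precise analysis is the default.

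It is also fair that the gain shrinks to about 2 points of power at correlation .8, and that no correlation is given. The low correlation for speech is an inference from the change of device and the time gap, not a figure.

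Three stronger readings are tempting but not supported:
- *The plan cannot show when or in which direction the arms differ.* The same sentence lists pairwise contrasts, which can show both.
- *Treatment expectations will be adjusted for only if they prove related to outcome.* The article says they will be analysed in relation to outcomes and may be controlled for. That is loose, but it states no selection rule.
- *A single 1-df contrast at T1 is a free gain.* It is a bet on the effect pattern, as the growing-effect case shows (.27 v .53).

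**Conclusion.** The point holds as one of efficiency. Using the T0 score as an adjuster rather than as a third outcome level gains precision from data already collected. With 18 per arm and a sustained 0.8 SD difference, the gain is about 2 points of power at correlation .8, 6 to 7 at .7, 17 to 18 at .5, and 21 to 22 at T0-post .3 with T1-T2 .7. These figures rest on assumed correlations, approximate normality, complete data and an effect of equal size at T1 and T2. The gain is smaller if the effect is present at T1 only. It is likely to matter most for speech, but its size there cannot be fixed from the article.

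**What to change.** In Data analysis and statistical methods, replace the test with a model in which T1 and T2 are the outcomes, T0 is a covariate, and the fixed effects include group, visit and group x visit. Equivalently, keep all three visits but constrain the group means to be equal at T0.

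In the covariate model, the treatment test is the joint 2-df test of the T1 and T2 group differences (group and group x visit together). The group x visit term alone asks only whether the difference changes between T1 and T2. Report the between-group contrasts at T1 and T2 from this model.

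For speech, which is tested before implantation through both unilateral and bilateral hearing aids, name one T0 aided condition as the covariate.

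Making a 1-df contrast at T1 the sole primary test is optional. It should be chosen only if the investigators are ready to commit to that effect pattern.

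The cost is a change of wording. No new data, visits or participants are needed, and the recruitment target can stay as it is.
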